### Statistical analysis

2.9

The continuous data will be presented as mean ± standard deviation or median (interquartile interval) according to a statistical distribution. The normality will be studied by the Shapiro–Wilk test. The categorical variables will be presented with the number of patients and percentages. To determine prognostic factors for EN intolerance, we will start by univariate analyses using the log-rank test for categorical variables and by the Cox model for continuous parameters. Then, a multivariable analysis will be performed using the Cox proportional-hazards model. The covariates will be determined according to univariate results and their clinical relevance. Kruskal–Wallis rank-sum test will be used to compare species abundance in the gut microbiota data. All tests are bilateral, and *P* < .05 is considered statistically significant. Data related to the gut microbiota will be statistically analyzed by R software, and other data performed by SPSS23.0 (SPSS, Inc, Chicago, IL) software.

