### Estimation of sample size

2.8

According to the preliminary survey results, the current EN intolerance rate in the ICU of Beijing Tiantan Hospital is 57%. It is expected that the EN intolerance rate will decrease to 40% after adjusting the EN feeding scheme according to the composition of intestinal flora. The 2-sided type I error rate is 5%, and the power is 90%. In consideration of 10% attrition, the final sample size is ∼100 (89/0.9) cases.

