In recent years, researchers have proposed that particular gut microbiota signatures could be used to predict the occurrence, development, or clinical outcomes of certain diseases. Agudelo-Ochoa et al^[38]^ found that the gut microbiota of ICU patients with sepsis has an increased abundance of microbes tightly associated with inflammation and the abundance of pathogenic species, such as *Enterococcus spp*., was differentially increased in sepsis patients who died. Reitmeier et al^[39]^ demonstrated in 1976 subjects of a German population cohort (KORA, a prospective cohort in the region of Augsburg designed to understand the role of genetic, lifestyle, and environmental factors in disease progression including metabolic diseases) that specific microbiota members show 24-hour oscillations in their relative abundance and identified 13 taxa with disrupted rhythmicity in type 2 diabetes. Tang et al^[40]^ identified a microbiome signature containing 21 OTUs that can potentially predict postoperative Hirschsprung-associated enterocolitis with ∼85% accuracy.

The overarching objective of this study is to establish a predicting and monitoring system for EN intolerance in ICU patients based on gut microbiota. Focusing on the relationship between gut microbiota and the host intestinal environment, this project will study the structure and composition of gut microbiota in ICU patients using 16S rRNA sequencing technology, taking patients with trauma and postoperative acute stress as the research subjects. The results of this study will help us to find out the potential probiotics as dietary supplements to improve EN intolerance. The limitation of this study is the single-center design, which may potentially cause recruitment biases.

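### Selecting Cox covariates by their univariate results, with about 51 expected events, is likely to over-fit and does not suit the stated predictive aim

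*Protocol article*

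**What the plan says.** Section 2.9 sets out two steps for finding factors prognostic for EN intolerance. First, "we will start by univariate analyses using the log-rank test for categorical variables and by the Cox model for continuous parameters". Second, a multivariable Cox proportional-hazards model, for which "The covariates will be determined according to univariate results and their clinical relevance". A two-sided P below .05 "is considered statistically significant"; no separate threshold is given for the screening step. For species abundance the section names the Kruskal–Wallis test and does not say whether taxa also become Cox candidates.

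The purpose is predictive. Section 2.1 (Study aim) wants microbial markers that predict intolerance, and the Discussion gives the overall objective as to "establish a predicting and monitoring system for EN intolerance in ICU patients based on gut microbiota".

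Section 2.8 gives the planning figures: "the current EN intolerance rate in the ICU of Beijing Tiantan Hospital is 57"%, an assumption that "the EN intolerance rate will decrease to 40% after adjusting the EN feeding scheme", 5% two-sided error and 90% power, and 89 patients before allowance for attrition, or about 100 enrolled.

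**The concern.** A variable is more likely to pass a univariate screen when sampling error happens to push its estimate away from zero. If the survivors are then fitted and tested in the same patients, that error stays in the estimates. Three things follow:

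- Retained coefficients are biased away from zero.
- The final P-values and confidence intervals ignore the selection and are too optimistic.
- Factors that matter only jointly with others can be dropped at the first step.

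The fewer the events per candidate, the worse this becomes.

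For a marker-finding study this matters beyond the paper. The Abstract and Discussion expect the markers to lead to a new nutrition strategy and to candidate probiotics. A factor retained by chance would carry over into both.

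**Working it through.** **Reproducing the plan's sample size.** The stated 89 matches a one-sample test of a proportion with p0 = 0.57 and p1 = 0.40 (section 2.8):

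n = [1.960·√(0.57·0.43) + 1.282·√(0.40·0.60)]² / (0.57 − 0.40)² = 88.4, so 89. Then 89/0.9 = 98.9, or about 100.

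The figure reproduces. It is sized to detect a fall in the intolerance rate, not to develop a prediction model.

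**Expected events.** 0.57 × 89 = 50.7, about 51. If all 100 are evaluable, the figure is 57.

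**Possible candidates.** The lists in sections 2.4.1 and 2.4.2, leaving out the ID, the clinical outcomes and response to feeding, give 9 demographic + 6 surgical + 9 laboratory + 3 severity scores + 10 drug classes + 10 nutritional = 47. If all are screened, there are 50.7/47 ≈ 1.1 events per candidate.

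**Expected false selections.** With 47 independent noise candidates at P<.05, the expected number is 47 × 0.05 = 2.35. The chance of at least one is 1 − 0.95^47 ≈ 0.91.

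**Simulation of the planned type of model.** Each run had 89 patients, a 57% event rate and independent normal candidates unrelated to outcome. It applied a univariate Cox score test at P<.05, fitted a multivariable Cox model on the survivors, and computed the C-index in the same patients and in 500 new ones. There were 400 runs per row. C-index means are over runs that selected at least one variable.

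| Candidates | Mean selected | Runs selecting none | Apparent C (5th–95th percentile) | C in new patients |
|---|---|---|---|---|
| 10 | 0.5 | 61% | 0.60 (0.57–0.66) | 0.50 |
| 20 | 1.0 | 34% | 0.61 (0.57–0.66) | 0.50 |
| 50 | 2.6 | 7% | 0.64 (0.58–0.71) | 0.50 |
| 100 | 5.2 | 0.5% | 0.69 (0.62–0.76) | 0.50 |
| 200 | 10.4 | 0% | 0.76 (0.69–0.82) | 0.50 |

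A separate Cox simulation with exactly 47 candidates also gave about 0.64.

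**Sensitivity to the event rate.** At 40% (0.40 × 89 = 35.6 events), the apparent C was 0.67, 0.73 and 0.80 for 50, 100 and 200 candidates. Fewer events make the optimism larger.

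**The case against.** Several points on the other side are sound and limit the finding.

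- **Clinical relevance is also part of the rule.** The simulation has no such filter. With 10 to 20 candidates, 61% to 34% of noise runs selected nothing. Over-fitting is therefore likely but not certain.
- **The 47 variables are a data-collection list.** Nothing says every item is screened. Some overlap (weight, height and BMI; several liver tests; two lymphocyte measures), which lowers the effective number. About 1.1 events per candidate is the unfavourable end.
- **Taxa are not stated to enter the Cox model.** A reader might infer that hundreds of taxa are screened into it, but the article gives only Kruskal–Wallis for species abundance. The 100- and 200-candidate rows are therefore conditional.
- **Validation may be described elsewhere.** A reader might conclude that the study has no internal validation. The article is condensed and the full protocol and SAP are not shown, so its silence does not establish that.
- **The Cox analysis is described as a search for prognostic factors.** The article does not say that this model is itself the prediction system.

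What survives is the selection rule itself, which is stated text. Later detail could add validation around it, but the coefficients and P-values of a model selected this way remain biased while the rule stands. An analysis of prognostic factors needs valid estimates and P-values too.

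**Conclusion.** The point holds in this limited form. Choosing Cox covariates by their univariate results and testing them on the same patients, with about 51 expected events, is a poor basis for finding markers meant to predict intolerance. It is a stated method, not a missing detail.

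On pure noise the apparent C-index is about 0.64 if all 47 or so listed variables are screened, and 0.69 to 0.76 with 100 to 200 candidates, against a true 0.50. These figures assume P<.05 screening (the article gives this as the significance level, not as the screening threshold), independent candidates, and no clinical-relevance filter.

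A reader might go further and say that the plan will produce a model that looks accurate on noise. The documents do not support that. An apparent C of 0.64 is optimistic but modest, and higher values need candidate counts that the article does not state. A binary AUC from t-test selection and a linear score comes out higher (about 0.71 to 0.72 with 47 candidates, 0.84 with 147, 0.91 with 247), but that is not the planned model. The Cox figures are the ones to rely on.

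**What to change.** In section 2.9 and the SAP:

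1. Stop using univariate results to choose covariates. Name a small clinical set in advance, on clinical grounds and before outcome data are seen, sized to about 51 events. As plain arithmetic, 5 single-parameter covariates leave about 10 events each (51/5) and 10 leave about 5 (51/10).
2. State whether microbial features enter the Cox model. If they do, list the candidates and use a penalised Cox model, such as LASSO or elastic net.
3. Repeat every selection step inside each bootstrap sample or cross-validation fold.
4. Report the optimism-corrected C-index and calibration, and the gain over the clinical covariates alone if microbial features are added.

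Univariate results can still be reported as description. If the unseen SAP already covers steps 2 to 4, only the selection rule needs changing.

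The cost is revised wording and more computing, with no extra patients or samples. The reported accuracy will be lower, and closer to what new patients would show.

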### Study aim

2.1

The study aims to observe the effect of EN on the gut microbiota of ICU patients, and screen microbiological markers for predicting EN intolerance in ICU patients.

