#### Feces collection and preservation

2.5.1

Fecal samples will be collected on admission and days 3 and 7. For patients hospitalized in the ICU for longer than 14 days, an additional fecal sample will be collected on day 14. All fecal samples will be collected by inserting a sterile rectal swab into the anus 1 to 2 cm and rotating the swab 3 to 4 times. The swabs will be placed in a sterile Eppendorf tube and immediately stored in a refrigerator at −80°C until use.

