#### 16S rRNA sequence analysis

2.5.3

Operational taxonomic units (OTUs) will be clustered with a 97% similarity cutoff using UPARSE (a method for generating clusters from next-generation sequencing reads of marker genes, http://drive5.com/uparse/), and chimeric sequences will be identified and removed using UCHIME (an algorithm for detecting chimeric sequences, https://www.drive5.com/usearch/manual/uchime_algo.html). The taxonomy of the 16S rRNA gene sequence will be analyzed by RDP (Ribosomal Database Project) Classifier against the SILVA database (a web resource providing comprehensive, quality checked and regularly updated datasets of aligned small (16S/18S, SSU) and large subunit (23S/28S, LSU) ribosomal RNA (rRNA) sequences for all three domains of life (Bacteria, Archaea and Eukarya), https://www.arb-silva.de/). The alpha diversity will be calculated using Chao1, Shannon, and PD (Phylogenetic diversity) indexes based on the OTU profiles to estimate the richness and diversity of the samples. The weighted principal coordinate analysis will be performed based on UniFrac distances to measure community clustering.

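### No primary outcome, contrast, index or day is named, the one sized contrast is never analysed, and every test counts as significant at an unadjusted two-sided 5%

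*Protocol article*

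**What the plan says.** All references are to the protocol article.

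- **Aims (2.1).** Two aims in one sentence, not ranked there: "The study aims to observe the effect of EN on the gut microbiota of ICU patients, and screen microbiological markers for predicting EN intolerance". The Discussion later calls a system for predicting and monitoring EN intolerance the overarching objective.
- **Samples (2.5.1).** "Fecal samples will be collected on admission and days 3 and 7", with a further swab on day 14 for patients who stay in the ICU longer than 14 days.
- **Community measures (2.5.3).** "The alpha diversity will be calculated using Chao1, Shannon, and PD (Phylogenetic diversity) indexes". A principal coordinate analysis on UniFrac distances is added. No hypothesis test is attached to either.
- **Sample size (2.8).** The planning assumption is that "the EN intolerance rate will decrease to 40% after adjusting the EN feeding scheme according to the composition of intestinal flora", from a current rate of 57%, at two-sided 5% and 90% power. The result: "In consideration of 10% attrition, the final sample size is ∼100 (89/0.9) cases".
- **Analysis (2.9).** Log-rank and Cox univariate analyses and then a multivariable Cox model for prognostic factors of EN intolerance, and Kruskal–Wallis for species abundance. One rule governs them: "All tests are bilateral, and *P* < .05 is considered statistically significant".

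The article names no outcome, index, day or comparison as primary, labels nothing exploratory and gives no hierarchy.

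**The concern.** A two-sided 5% rule controls the false-positive risk of one test. It controls the risk of the study's main claim only if the plan says which test carries that claim. Here the plan does not say, and the same full alpha goes to every test.

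The sample-size section would normally show which contrast decides the study. In this article it does not: the contrast sized there belongs to neither aim and has no counterpart in section 2.9.

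Two things are at stake. First, an association between the gut community and EN intolerance could be reported from whichever measure and day crosses 5%, with a real error rate above the stated one. Second, the choice of day changes the meaning of the result. The Introduction cites data in which intolerance appeared on average within 3 days (range 1 to 12). A swab on day 7, and often one on day 3, may therefore follow the event and reflect it. Without a pre-named day, the reader cannot separate a planned predictive result from one selected after the data were seen.

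**Working it through.** **1. The plan's own figure.** Inputs from 2.8: 57%, 40%, two-sided 5%, 90% power, 10% attrition. For one sample against a fixed 57%:

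n = [1.960 × √(0.57 × 0.43) + 1.282 × √(0.40 × 0.60)]² / (0.57 − 0.40)² = 88.4, rounded up to 89.

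89 / 0.9 = 98.9, about 100. The stated figures reproduce. A two-group comparison of the same rates would need 180 per group, so the plan's number is the one-sample calculation.

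**2. Is that contrast analysed?**

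| Section | Content |
|---|---|
| 2.8 | Intolerance rate after the feeding scheme is adjusted to the flora, against 57% |
| 2.1 | Effect of EN on the microbiota; marker screening |
| 2.2 and 2.6 | Prospective cohort; care as usual |
| 2.9 | Prognostic-factor analyses; species abundance |

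No test of the rate against 57% is planned. The 89 supports no diversity contrast, and the analyses in 2.9 were not the ones sized.

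**3. How many community-level comparisons are open?** Three indices on three days make 9 index-by-day cells, and 12 with day 14. UniFrac as a fourth measure makes 12 cells over three days and 16 over four.

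**4. Family-wise error if the cells were tested.** Assumption: one comparison of tolerant with intolerant patients per cell, each at two-sided 5%. The article lists no such tests and gives no correlations. Under independence the chance of at least one false positive among k tests is 1 − 0.95^k. For correlated tests the figures come from 400,000 simulated draws of equicorrelated normal statistics.

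| Tests | Correlation 0 | 0.5 | 0.9 |
|---|---|---|---|
| 3 (three indices, one day) | 14.3% | 12.6% | 8.4% |
| 9 (three indices, three days) | 37.0% | 26.9% | 12.4% |
| 12 (three indices, four days) | 46.0% | 31.9% | 13.5% |

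The 12-test row is an upper case, because only long stayers give a day 14 swab. If a test were also attached to UniFrac, independence would give 46.0% for 12 tests (four measures, three days) and 56.0% for 16. With correlation 0.9 between measures and 0.7 between days, the figures are 19% and 23%.

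**5. After the fix.** One pre-named contrast at 0.05 has a false-positive rate of 5%. Holm over three tests uses thresholds 0.05/3 = 0.0167, 0.05/2 = 0.025 and 0.05, and keeps the family at 5%.

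**The case against.** **No tests on the indices are written down.** A reader might infer that all three indices and UniFrac are to be tested on every swab day at 5%. The article does not say so. The indices are calculated to describe richness and diversity, an ordination gives no P value by itself, and the only microbiota test named is Kruskal–Wallis on species abundance. This stands, so the table above is conditional. What remains is that the article promises to relate the microbiota and its changes to EN intolerance, and any test done for that purpose falls under the rule in 2.9.

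**The aims are not equal.** A reader might take the two aims in 2.1 as co-equal. The Discussion puts prediction and monitoring first. This also stands, but the Discussion names no index, day or test, so the deciding contrast is still open.

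**The detail may sit in a full protocol or analysis plan.** For an unmentioned index or day alone, this would be a complete answer. Here, however, the article states a decision rule for all tests and sizes a contrast that it does not analyse. Those are statements in the text, not gaps.

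**Later swabs can also predict or monitor.** Correct for some patients, given the 1 to 12 day range, so it would be too strong to say that a day 7 difference can never be predictive. The plan does not separate swabs taken before onset from those taken after it.

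**The wording is exploratory in tone.** The article speaks of screening markers. If that is the intention, labelling the analyses exploratory costs nothing, but a blanket significance rule says otherwise.

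**Conclusion.** The point holds in a limited form. The article names no primary outcome, contrast, index or time point, does not analyse the contrast it sized, and applies an unadjusted two-sided 5% to every test. A claim about the gut community and EN intolerance could rest on any measure and day.

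The size is conditional. With one test per index and day, the family-wise error is about 12% to 37% for nine tests and 8% to 14% for three indices on one day, over correlations from 0.9 to 0. Every scenario exceeds 5%, but the number of tests and the correlations are assumptions. A single figure such as 27% or 32% should not be quoted as a property of this plan: it needs both the assumed tests and a correlation of 0.5.

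The documents do not support saying that the indices and UniFrac are all tested at 5%, or that the aims are declared equal. Nor do they favour any particular index. False-discovery control across taxa is a separate matter and would leave index and day open.

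The study remains useful for screening markers. Until the deciding contrast is named, a headline result cannot be read at the stated 5%.

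**What to change.** In section 2.9, in line with the predictive objective in the Discussion:

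1. Pre-name one primary contrast with the admission swab as predictor of EN intolerance, tested at two-sided 5%. One pre-chosen alpha-diversity index, entered as a single coefficient in the Cox model, would do. Section 2.9 does not now say that diversity enters that model, so this must be written in. Alternatively, test all three indices at admission with Holm.
2. Label as exploratory the other indices, UniFrac, the day 3, 7 and 14 comparisons and the clinical prognostic factors. Report them as estimates with 95% confidence intervals and without claims of significance.
3. State in 2.8 that the 57% to 40% calculation does not size the primary contrast, or replace it with one that does.

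Items 1 and 2 are wording only: no extra patients, swabs or assays. The price is that significant results outside the primary contrast become hypothesis-generating. With Holm, the smallest of the three P values must also fall below 0.0167 before anything can be claimed. Under item 3, a new calculation could show that about 100 patients give less than 90% power for the chosen contrast. That would be better known before the data are analysed.

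### Section 2.9 judges the taxon-by-taxon marker screen at P < .05 with no multiplicity control stated, so about 5% of unrelated taxa tested would be called markers in each comparison

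*Protocol article*

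**What the plan says.** Section 2.1 gives as one of the study's two aims to "screen microbiological markers for predicting EN intolerance in ICU patients". The features come from 16S sequencing: "Operational taxonomic units (OTUs) will be clustered with a 97% similarity cutoff using UPARSE" (section 2.5.3). Swabs are taken repeatedly: "Fecal samples will be collected on admission and days 3 and 7" (section 2.5.1), with a day 14 sample for patients who stay in the ICU longer than 14 days.

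Section 2.9 has one sentence on testing the microbiota data: "Kruskal–Wallis rank-sum test will be used to compare species abundance in the gut microbiota data". It does not say which groups are compared, at which taxonomic rank, or at which sampling time. The next sentence sets the threshold: "All tests are bilateral, and *P* < .05 is considered statistically significant". The article does not mention adjustment for multiple testing, a limited set of candidate taxa, or confirmation in a second sample.

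**The concern.** A marker screen asks the same question of many taxa. A threshold of .05 limits the error of one test, not of the list the screen produces. The only decision rule in the article covers all tests, so it takes in the taxon tests too. A reader who applied section 2.9 as printed would call any taxon with P below .05 significant.

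The list of taxa is a central product of the study. The abstract's conclusions and the Discussion look ahead to a system for predicting intolerance and to candidate probiotics. If the list mixes real and chance associations with no stated error rate, later work may follow up microbes that have nothing to do with intolerance.

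**Working it through.** **The plan's own figure.** The only calculation in the article is the sample size in section 2.8 (57% falling to 40%, two-sided 5%, power 90%). It reproduces as a one-sample test of a proportion:

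n = [1.960 × √(0.57 × 0.43) + 1.282 × √(0.40 × 0.60)]² / 0.17² = 88.4, so 89; and 89/0.9 = 98.9, about 100.

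That figure concerns a fall in the intolerance rate. It says nothing about the error rate or power of the taxon screen.

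**Inputs for the screen.**
- Threshold: 0.05 two-sided for each test (section 2.9).
- Number of taxa tested, m: not given. Assumed values are 20, 50, 100 and 500.
- State of nature: no taxon truly associated.

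**Formulas.** Expected false markers per comparison = 0.05 × m, whatever the correlation between taxa. Chance of at least one, if the tests are independent = 1 − 0.95^m.

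| m (assumed) | 0.05 × m | 1 − 0.95^m |
|---|---|---|
| 20 | 1 | 64% |
| 50 | 2.5 | 92% |
| 100 | 5 | 99.4% |
| 500 | 25 | >99.9% |

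**Effect of correlation.** Take two-sided normal test statistics with a common pairwise correlation. At a correlation of 0.3, the chance of at least one false marker falls to 81% for 50 taxa and 94% for 100. At 0.5 it falls to 62% and 78%. The expected counts stay at 2.5 and 5.

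**Simulation check.** Null Kruskal–Wallis tests were simulated on zero-inflated abundances in 89 patients, split 51/38 (0.57 × 89 = 50.7), with 150 replicates and a latent correlation between taxa of 0 or 0.3. Mean false positives were 2.5 and 2.3 for 50 taxa, 5.1 and 5.2 for 100, and 14.8 and 15.0 for 300. These agree with 0.05 × m.

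**Several sampling times.** If the tests were repeated at three or four times, the expected number of false-positive tests for 100 taxa would be 15 or 20. Some would hit the same taxon twice. With independent times, the expected number of distinct false taxa is 100 × (1 − 0.95³) = 14.3 or 100 × (1 − 0.95⁴) = 18.5. Because samples from one patient are likely to be correlated, it would probably be lower. The article does not say that the tests are repeated in this way.

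**After the fix.** With Benjamini–Hochberg at 5% in the same simulations, the chance of declaring any taxon was between 3% and 5% for 50, 100 and 300 taxa.

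**The case against.** The strongest reply is that this is an omission, not an error. The article condenses a fuller plan, the threshold sentence is a stock closing line, and it does not say that P is unadjusted. Benjamini–Hochberg adjusted P values could be compared with .05 without breaking it. This is right to the extent that a reader might infer that section 2.9 rules out a correction, and it does not. But the sentence is the only rule given, it covers all tests, and it directly follows the sentence on species abundance. Applied as printed, it gives the uncontrolled screen.

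Other parts of the reply also stand, and they limit the point:

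- The number of taxa is unknown, and with 20 taxa a false marker is likely rather than near certain. The 99.4% figure needs about 100 taxa and independent tests.
- The groups are not named. The link to EN intolerance comes from the stated aim. The expected count holds for any grouping under its own null.
- A reader might add the three alpha-diversity indices to the number of tests. Section 2.5.3 only says they are calculated, and no test of them is specified.
- A reader might conclude that the marker list could not be told from chance. That goes too far: a count of significant taxa well above 0.05 × m would be evidence of real signal, although it would not show which taxa carry it.
- Care is not altered by the study, and the correction can be made at analysis without new data.

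**Conclusion.** The point holds. Section 2.9 applies P < .05 to every test, including the taxon comparisons that serve the marker aim, and states no control of multiplicity. If no taxon is truly associated, each comparison is expected to give 0.05 × m false markers, which is 1 to 25 over the assumed range of 20 to 500 taxa. That count does not depend on independence; the chance of at least one does. If some taxa are truly associated, the list will hold true and false markers together, with no stated limit on the false share.

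The documents do not support saying that every taxon will be declared significant, that false markers are certain whatever the number of taxa, or that the number of falsely named microbes triples or quadruples over the sampling times. They also give no reason to withdraw P < .05 from the Cox analyses of prognostic factors.

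**What to change.** Amend the threshold sentence in section 2.9 along these lines: for comparisons of taxon abundance, P values will be adjusted by the Benjamini–Hochberg method within each family, a family being all taxa of one taxonomic rank in one comparison, and a taxon will be called a marker only if its adjusted P (q) is below .05; for all other analyses, two-sided P < .05 applies as now. The comparisons have to be named for the families to be defined, so the same edit should state the groups and sampling times to which the Kruskal–Wallis test applies. If the full analysis plan already contains such a rule, the published sentence should be brought into line with it.

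The change needs no new patients, samples or sequencing, and little extra programming. Its cost is that fewer taxa will be declared significant, so some real but weak associations will be missed. The control holds within each family and not across all of them, so the number of families should be reported.
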